# Efficacy of Traditional Chinese Medicine Combined Online Group Psychotherapy (TCM-eRhab) on improving quality of life and relieving psychological burden for colorectal cancer survivors: a study protocol for a phase-II randomized controlled trial

**DOI:** 10.1186/s12906-024-04533-y

**Published:** 2024-07-30

**Keywords:** Colorectal cancer, Psychological burden, Quality of life, Traditional Chinese medicine, Randomized controlled trial

## Abstract

**Background:**

More than 50% of colorectal cancer(CRC) patients experience cancer-related psychological burden after radical surgery, which can seriously affect their physical wellness, quality of life and even survival outcomes. Our research team developed a six-week Traditional Chinese Medicine Combined Online Group Psychotherapy (TCM-eRhab) and proved its efficacy on relieving cancer-related anxiety, depression and fear of cancer recurrence though phase I single arm clinical trial (*n* = 40). Large sample size randomized controlled clinical trial(RCT) is necessary to further evaluate TCM-eRhab’s role on improving quality of life and survival outcomes among this population.

**Methods:**

We design a phase II RCT study, in which 210 CRC patients who have received radical surgery (stage I-III) will be recruited. Eligible patients will be randomly assigned to TCM-eRhab group or usual care group by 2:1 ratio. Patients in the intervention group will receive the structured TCM-eRhab program for six weeks, while patients in control group will receive usual care only. The primary outcomes are quality of life, severity of anxiety, depression and fear of cancer recurrence. Cancer recurrence rate will also be calculated according to long term follow-up data.

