## Material and methods

### Study design and setting

This is a prospective, open label, parallel group randomized clinical trial with interventions designed to assess quality of life, anxiety, and depression outcomes according to Traditional Chinese Medicine Combined Online Group Psychotherapy(TCM-eRhab) program among early-stage CRC patients. We plan to enroll 210 patients in Xiyuan Hospital, China Academy of Chinese Medical Sciences(CACMS) and Beijing Cancer Hospital. During the screening visit, study procedures are explained and written informed consent is obtained by study researcher. Figure 1 depicts the flow of patients through the study. Trial registration is available at International Traditional Medicine Clinical Trial Registry (ITMCTR2022000041). The protocol has been approved by Ethics Committee of Xiyuan Hospital, CACMS(2022XLA079-1).

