#### Sample size

Previous studies evaluating TCM-eRhab program for early-stage CRC patients reported a mean difference of 66.1 ± 10 points after the intervention on the QOL-C30 scale. In addition, the evidence reported on the average of scores of QOL-C30 scale for CRC patients with early-stage was 61.5 ± 10 points. In order to provide 80% power to detect this clinically meaningful difference, using a two-sided test with alpha = 0.05 and assuming that 15% of patients opt out, we need to approach approximately 210 patients (TCM-eRhab intervention group:140 patients, Control group: 70 patients).

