## Discussion

TCM-eRhab program as an online mind–body group therapy intervention has the potential to address complex constellation of symptoms. Meanwhile, TCM-eRhab program integrates treatment elements of TCM psychotherapy and modern psycho-oncology. By carrying out this randomized controlled trial, it will facilitate the development of current clinical practice towards innovative models of integrative Chinese and western rehabilitation and optimize the modern mind–body intervention methods.

The main objective of this study is to assess the evidence of TCM-eRhab program for improving CRC patient’s quality of life after radical surgery as well as benefiting their survival outcomes especially DFS. According to current ASCO guideline, promoting health condition, treating cancer related symptoms and preventing cancer recurrence are all major components of survivorship care for CRC patients. However, there is still lack of an effective and efficient intervention that could meet more patients’ needs at the same time. Thus, our study results will have profound meaning for the development an integrative intervention model of cancer survivorship care for CRC survivors.

This study will conduct online group therapy for patients which contains potentially unique therapeutic advantages such as encouraging expression, peer-support, coping skills, mindfulness practice and emotional expression. In addition, each patient will receive a comprehensive psychological, symptom and survivorship care needs assessment that is carried out at the beginning of the therapy, so that individualized TCM and supportive care plans can be integrated into the related session. So far, several studies have proved that education on lifestyle and health behavior has positive impact on CRC patients’ quality of life [20, 21]. To the best of our knowledge, the current study is one of the first to integrate methods and opinions of TCM into such education program and group therapy.

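### Four outcomes are labelled primary with no success rule, while the sample size spends the full two-sided 0.05 and the 80% power on the QLQ-C30 alone

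*Protocol article*

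**What the plan says.** **Outcomes.** The abstract (Methods) reads: "The primary outcomes are quality of life, severity of anxiety, depression and fear of cancer recurrence". In the body, the Primary outcomes section contains QLQ-C30, SAS, SDS and FCRI. Secondary outcomes begin only after these four.

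**Analysis.** The Statistical analysis section describes one primary analysis. It covers the QLQ-C30 and the self-reported psychological scales together, as a between-group difference after the intervention. It gives no order, no division of alpha and no definition of a positive trial.

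**Sample size.** The only alpha in the article is in this section: "using a two-sided test with alpha = 0.05". It belongs to a calculation on the QLQ-C30, described as "In order to provide 80% power to detect this clinically meaningful difference". No expected effect or power is given for SAS, SDS or FCRI.

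**Outcome list elsewhere.** Study design and setting speaks of "interventions designed to assess quality of life, anxiety, and depression outcomes", without fear of recurrence. The primary aim in the Introduction puts quality of life first and psychological burden beside it.

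**The concern.** The number of primary outcomes and the alpha behind the sample size are both fixed in this article, and they do not match. Four outcomes carry the primary label. One of them has been given the whole 5% and all the stated power.

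The pilot makes this more than a formality. According to the abstract and Introduction, that single-arm study (n = 40) found reductions in fear of recurrence, anxiety and depression but no significant change in quality of life. The one outcome with stated power is thus the one that has not yet moved, and the three without it are those that have. The new trial is open label against usual care, and all four outcomes are self-reported. As the text stands, quality of life could miss, one of the other scales could reach a nominal p < 0.05, and nothing written would prevent that being reported as a positive primary result.

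**Working it through.** **1. Inputs**
- Sample size section, intervention mean and SD: "reported a mean difference of 66.1 ± 10 points after the intervention on the QOL-C30 scale". This is worded as a difference but is usable only as a mean.
- Sample size section, comparator mean and SD: "scores of QOL-C30 scale for CRC patients with early-stage was 61.5 ± 10 points".
- Sample size section: two-sided alpha 0.05, power 80%, 140 + 70 = 210 patients, and loss as in "assuming that 15% of patients opt out".
- Randomization and allocation: 2:1.
- Assumed, not in the article: the correlations between the four test statistics.

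**2. The plan's own figure**

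Difference = 66.1 − 61.5 = 4.6; SD 10; standardised effect d = 0.46.

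Control n = (1 + 1/2) × [10 × (1.960 + 0.842) / 4.6]² = 55.6, so 56.
- Normal approximation: 56 / 0.85 = 65.9, so 66 controls and 3 × 66 = 198 in total.
- t-test: 57 controls; 57 / 0.85 = 67.1, so 68, and 3 × 68 = 204 in total.

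The t-test total is within 3% of 210. The arithmetic is sound for one outcome at the full 0.05.

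**3. Any-one-of-four rule, each outcome at 0.05, all four nulls true**

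Independent tests: 1 − 0.95⁴ = 0.1855. For correlated tests, four two-sided z-tests with a common correlation were simulated (1,000,000 draws):

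| Assumed correlation | Chance of at least one false positive |
|---|---|
| 0 | 18.5% (exact) |
| 0.3 | 17.4% |
| 0.5 | 15.6% |
| 0.7 | 13.0% |
| 0.8 | 11.4% |
| 0.9 | about 9% |

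This counts one test per outcome. The QLQ-C30 has several scales and is collected at weeks 2, 4 and 6, so testing those separately would raise the figures.

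**4. Equal alpha split (0.05 / 4 = 0.0125 each)**

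Evaluable patients: 0.85 × 140 = 119 and 0.85 × 70 = 59.5.

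d / √(1/119 + 1/59.5) = 0.46 / 0.1588 = 2.897.
- At 0.05: Φ(2.897 − 1.960) = 0.826; t-test 0.818 to 0.822 (59 or 59.5 controls).
- At 0.0125: Φ(2.897 − 2.498) = 0.655; t-test 0.641 to 0.646.

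QLQ-C30 power falls from about 82% to about 64–65%. To restore 80%:
- Normal approximation: 80 controls; 80 / 0.85 = 94.1, so 95, and 3 × 95 = 285 in total.
- t-test: 81 controls; 81 / 0.85 = 95.3, so 96, and 3 × 96 = 288 in total.

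**5. All-four rule**

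The error stays at or below 5%, but the chance of all four succeeding cannot exceed the QLQ-C30's own 82% or so. As an illustration, if the other three also had 82% power and the tests were independent, it would be 0.82⁴ = 45%. The article gives nothing from which the real figure could be computed.

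**6. QLQ-C30 tested first at 0.05, the others only if it succeeds**

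The error is held at 5% and the sizing in step 2 stays valid. The other three outcomes then depend on the first, which the article does not say.

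**The case against.** The strongest reply is that this is a condensed article with no analysis plan shown, and that testing order and multiplicity procedures are commonly left to that plan. This stands in part. A reader might infer that the tests are unadjusted and that the trial's false-positive rate is therefore 13–19%. The article supports neither as a flat statement. It nowhere says the tests are unadjusted, it states no any-one-of-four rule, and it gives no correlations. At correlations of 0.8 to 0.9 the figure is about 9–11%, and under an all-four or QLQ-C30-first rule there is no inflation.

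A reader might also infer that the stated aim is quality of life alone, so that the psychological scales were never meant to be primary. The text does not bear that out. The primary aim in the Introduction adds relief of psychological burden. In the Discussion, the sentence beginning "The main objective of this study is to assess the evidence of TCM-eRhab program for improving CRC patient" goes on to quality of life and then to survival outcomes. Only the sample size is confined to the QLQ-C30.

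What the reply does not remove is the mismatch between things the article does state. A later plan cannot split alpha equally without making the stated 80% power untrue. It cannot require all four outcomes without power that nobody has shown. It can put the QLQ-C30 first, but that changes the standing of three outcomes now called primary.

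**Conclusion.** The point holds as a mismatch: four outcomes are labelled primary, one is sized, and no rule connects them. The sample size is not miscalculated; it simply covers one outcome of the four.

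The size of the error problem is conditional. If any one outcome at 0.05 suffices and all four nulls are true, the false-positive chance runs from 18.5% (independence) to about 9% (correlation 0.9), against a nominal 5%. With an equal split, QLQ-C30 power is about 64–65% instead of the stated 80%, assuming a difference of 4.6, SD 10 and 15% loss. Of the rules considered, only testing the QLQ-C30 first both controls the error and leaves the sample size paragraph true. The article should say so if that is the intention.

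**What to change.** - Name one QLQ-C30 score at week 6 as the single primary endpoint, tested at two-sided 0.05. It must be a specific scale, namely the one on which the 66.1 versus 61.5 sizing rests. The instrument has functional, global health and symptom scales, so naming the QLQ-C30 alone would leave multiplicity inside the primary endpoint.
- Make SAS, SDS and FCRI key secondary endpoints, tested in a fixed order or by Holm, and only if the primary succeeds.
- Use the same list in the abstract (Methods), the aim in the Introduction, Study design and setting, the Primary outcomes section with its scale subsections, and Statistical analysis.
- Settle this before outcome data are analysed, since a hierarchy chosen afterwards would not be credible.

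The cost is wording in the protocol and analysis plan plus a registry update; no more patients are needed. The downside is that three scales lose the primary label and cannot be claimed as confirmatory if quality of life misses. If the sponsor wants to keep four primaries, the alternatives cost more: about 285–288 patients to keep 80% QLQ-C30 power under an equal split, or an all-four rule with power shown for every outcome.

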**Discussion:**

As one of the first RCTs to evaluate the impacts of TCM combined psychological therapy to improve CRC patients’ quality of life after surgery, the results from this study will provide innovative knowledge and evidence on integrating TCM into CRC survivorship care and mind–body intervention model.

## Introduction

Colorectal cancer(CRC) accounts for more than 55,000 new cancer survivors and more than 29,000 deaths per year in China [1]. The 5- year survival rate is 60%-80% for early-stage colorectal cancer. Thus, attenuating postoperative recurrence risk is the best possible chance of cure for CRC patients. For early-stage CRC patients, surgical resection and adjuvant therapy is the curial curative intervention. However, cancer survivors are left with long-term physical and psychosocial morbidities because of cancer treatments and worries on cancer recurrence, which would eventually impair their quality of life [2]. Anxiety is one of the most common psychological symptoms, which’s prevalence rate among CRC patients was up to 29.0%, especially in patients with ostomy. In addition, the change of cognitive behavior leads to patients’ incorrect or distorted understanding, negative views and attitudes towards themselves [3]. Meanwhile, many studies have shown a strong correlation between cognitive intervention disturbance and anxiety [4, 5]. Consequently, psychosocial supports and symptom management for CRC survivors after radical surgery are essential to help them return to normal life.

According to NCCN guidelines, screening for cancer survivors’ psychological burden and providing education, group session and psychotherapy are recommended [6]. Existing studies have showed that cognitive behavior therapy, group courses and reminiscence therapy were effective to reduce CRC survivors’ fear of cancer recurrence(FCR) and psychological symptoms [7]. Growing evidence is also demonstrating that certain integrative oncology interventions, such as yoga, meditation and acupuncture could be valuable to wholistically promote CRC survivors’ rehabilitation on both body and mind [8, 9]. However, the level of evidence is still insufficient to apply these interventions into clinical practice guidelines and standard of cancer care.

Traditional Chinese Medicine(TCM) is an important component of integrative medicine, which could provide valuable guidance on lifestyle and coping skills for CRC survivors after surgery. Previously, our research team had developed an online program in which TCM theories and methods were integrated into conventional group psychotherapy(TCM-eRhab) [10]. Through pilot phase I clinical study, we preliminarily proved that the six-week TCM-eRhab program was feasible for clinical utilization and could significantly reduce CRC survivors’ FCR and psychological symptoms including anxiety, depression and insomnia. We also found that such intervention also could modulate certain gut microbiome that associated with psychological disorders. However, statically significant changes on quality of life had not been observed after intervention due to limitation on small sample size of our pilot study (*n* = 40). Thus, although TCM-eRhab has a significant potential as an effective intervention for CRC survivors, further evaluation in larger RCT trials on TCM-eRhab’s efficacy for their postoperative quality of life, anxiety and depression is required.

The primary aim of this current RCT study is to evaluate TCM-eRhab’s role on improving quality of life among CRC survivors while relieving psychological burdens when compared with usual care control group. We also plan to assess its association with patients’ survival outcomes especially disease-free survival and discover the potential beneficial population of such intervention.

## Material and methods

### Study design and setting

This is a prospective, open label, parallel group randomized clinical trial with interventions designed to assess quality of life, anxiety, and depression outcomes according to Traditional Chinese Medicine Combined Online Group Psychotherapy(TCM-eRhab) program among early-stage CRC patients. We plan to enroll 210 patients in Xiyuan Hospital, China Academy of Chinese Medical Sciences(CACMS) and Beijing Cancer Hospital. During the screening visit, study procedures are explained and written informed consent is obtained by study researcher. Figure 1 depicts the flow of patients through the study. Trial registration is available at International Traditional Medicine Clinical Trial Registry (ITMCTR2022000041). The protocol has been approved by Ethics Committee of Xiyuan Hospital, CACMS(2022XLA079-1).

**Fig. 1 Fig1:**
[figure not shown]
Participant Flow

### Inclusion criteria/Exclusion criteria

The trial will be performed with CRC patients who meet the following eligibility criteria: between 18 and 75 years of age; CRC patients who have undergone radically surgery and histologically confirmed AJCC TNM stage I, II and III disease. To ensure the communication is fluency for CRC patients, patients should be signed written informed consent.

As the study has a significant focus on the stage I-III CRC patients, if the patients have had any evidence of metastatic disease, then they will be excluded from the study. Patients who have history of clinically relevant psychiatric disability (e.g., severity personality disorders), precluding informed consent. If either person is unable to have a good compliance, they will be excluded from the study.

### Randomization and allocation

Following baseline assessment and registration, patients will be randomized in a 2: 1 ratio to either the TCM-eRhab program or to the normal usual care control group, using a computer-generated randomization list. Randomization will be overseen by research assistant, who will have no direct involvement in implementing the trial. Randomization is stratified by clinical center.

### Interventions

#### TCM-eRhab intervention group

The treatment will be jointly conducted by the department of psychology rehabilitation at Beijing Cancer Hospital, TCM-psychology department at Clinical Basic Research Institute of CACMS and TCM-oncology department at Xiyuan hospital. The feasibility of this protocol has been established by our previous trial, which will last for 6 consecutive weeks, once a week, lasting 60 min to 90 min each. The intervention protocol will be divided into six subjects, namely (1): Nice to meet you. (2): How to manage our symptoms? (3): How to manage our emotions? (4): How to be friend with our body? (5): How to support out family and loved ones? (6): How to plan out future and farewell! The content of TCM-eRhab in each week is detailed in Table 1. Then, the physical symptoms of patients will be personalized treatment by the TCM-oncologist and psychology therapist. The physical symptoms management of TCM and western medicine intervention in Table 2.

**Table 1 Tab1:** Session structure of TCM-eRhab program

**Period**		**Subjects**	**Intervention instructions**	**Technics**
**Week 1**	**Initial Phase**	*Session1:* Nice to meet you	Self-introduction; What is the aim rehabilitation in TCM concept (harmony); Mindfulness practice; guide patients to care themselves and share their feelings	Expression support
**Week 2**		*Session2:* How to manage our symptoms?	How to modify lifestyle after CRC diagnosis? How to use TCM to preserve life? Why we experience symptoms and how could we use TCM to manage them?	Cognitive Training;
**Week 3**	**Work Phase**	*Session3:* How to manage our emotions?	Do you fear of cancer recurrence? How could we manage emotion and stresses? Concentration practice. Acupoints and acupressure	Expression support
**Week 4**		*Session4:* How to be friend with our body?	Can you communicate with your body? Organ scan and mindfulness practice	Cognitive Training
**Week 5**	**Final Phase**	*Session5:* How to support out family and loved ones?	Anything changed on your family and social support after cancer diagnosis? Five most important things in your life. Relax practice	Cognitive Training
**Week 6**		*Session6:* How to plan out future and farewell!	Love mindfulness practice; future plan; lucky diary; farewell	Expression support

**Table 2 Tab2:** The physical symptoms management of TCM and western medicine intervention

Syndromes	Instrument	TCM-intervention	Western Medicine-intervention
Defecation obstacles	FACT-C	(1) The TCM syndrome differentiations. (2) Acupuncture (3) Acupoint pressure therapy	(1) Intestinal flora regulator. (2) Prokinetic agents
CIPN	CIPN-20	(1) The TCM syndrome differentiations. (2) Acupuncture (3) Chinese herb bath	(1) Neurotrophic drugs. (2) Psychoactive drugs
Sleep disturbance	PSQI	(1) The TCM syndrome differentiations. (2) Acupuncture (3) The TCM Five-element Music Therapy	(1) Cognitive training. (2) Psychoactive drugs. (3) Meditation and relax training
Cancer related fatigue	BFI	(1) The TCM syndrome differentiations. (2) Tai Chi and Qigong	(1) Relax training. (2) Exercise training
Anxiety and Depression	HADS	(1) The TCM syndrome differentiations. (2) Acupuncture (3) The TCM Five-element Music Therapy	(1) Psychological consultation. (2) Anti-anxiety Anti-depressant. (3) Meditation and relax training

#### Usual care (Control) group

The control group will not be invited to participate in the TCM-eRhab intervention group at the first six weeks. However, they will be compensated with TCM-eRhab treatments afterwards according to their own willingness. According to NCCN guideline, patients will do laboratory chemistries plus complete blood count (CBC), tumor markers, abdominal US (ultrasound) and CT scan during the first 3 years.

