**Efficacy parameters**							
SAS	√	√	√	√			
SDS	√	√	√	√			
FCRI	√	√	√	√			
QLQ-C30	√	√	√	√			
TCM-SS	√	√	√	√			
TCM-SDS/TCM-KDS	√	√	√	√			
CaSUN	√	√	√	√	√	√	√
Caner recurrence/other outcome events					√	√	√

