### Secondary outcomes

As secondary outcomes, The Cancer Unmet Needs (CaSun), Traditional Chinese Medicine syndrome scale (TCM-SS) and TCM spleen deficiency scale (TCM-SDS) will be applied. Another secondary efficacy endpoint of the study is Disease Free Survival (DFS), defined as the time from the date of randomization up to the date of first local, regional, or distant relapse. The follow-up will begin when the patient completes treatment phase. The follow-up visits will be done every year lasting for 3 years. Patients will do abdominal US (ultrasound) and CT (Computerized Tomography) and conduct the information including lifestyle, psychological state, and social relations.

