Experimental studies found that the combination of social interactions and cognitive stimulation regulated serum inflammatory factors, intestinal mucosal inflammatory factors and hypothalamic ghrelin levels [22, 23]. Some TCM herbal medicine, for example, Xiaoyaosan was found to be effective on preventing cancer cell progression and ameliorating gut dysbiosis through CRC mice model with chronic stress [24]. Our previous phase I trial also demonstrated that TCM-eRab intervention could modulate CRC survivors’ gut microbiome which had association with certain mental disorders. In the current trial, more mechanism on gut-brain axis interaction and CRC’s survival outcome are expected to be carried out.

There are some limitations on the current study design and certain obstacles for the administration of the clinical trial. First, as a behavioral study, it is unrealistic to conduct blind method, but we will use patient-reported outcome measurement to avoid investigator evaluation bias. Second, willingness to participate in the current trial is one of the major concerns for patients’ enrollment. According to an existing study, more than 60% CRC patients were not willing to participate in psychological intervention due to no perceived needs, older age and longer time since diagnosis [25]. Thus, in our study, we need to pay more attention on the balance between effectiveness of enrollment and population selection bias. Third, patients’ compliance of six-week intervention is also an important challenge for our study. We will record patients’ participation for each session and encourage them to comply with the protocol.

In conclusion, in this phase II randomized controlled clinical trial, we will evaluate the efficacy of an innovative model of online group psychotherapy, TCM-eRab on CRC survivors’ quality of life and survival outcomes after surgery. The implementation of the trial will help more CRC patients cope with their symptom burden and acquire guidance on healthy lifestyle by utilizing concepts and methods of TCM.

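### Controls may take TCM-eRhab after week 6, so DFS and the year 1–3 CaSUN values compare an immediate with an optional delayed offer, which does not fit the survival claim in the Discussion

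*Protocol article*

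**What the plan says.** - **Control arm.** The section on the usual care group says: "The control group will not be invited to participate in the TCM-eRhab intervention group at the first six weeks". The next sentence reads: "However, they will be compensated with TCM-eRhab treatments afterwards according to their own willingness". No expected uptake or timing is given.
- **DFS.** Under Secondary outcomes, DFS is a secondary efficacy endpoint, "defined as the time from the date of randomization up to the date of first local, regional, or distant relapse". On follow-up, the same section says: "The follow-up visits will be done every year lasting for 3 years".
- **Schedule.** In Table 3 the row "Caner recurrence/other outcome events" is ticked at years 1, 2 and 3 only. CaSUN is ticked at baseline, weeks 2, 4 and 6, and years 1, 2 and 3. QLQ-C30, SAS, SDS and FCRI stop at week 6.
- **Aims.** The Introduction gives quality of life and psychological burden as the primary aim. It then adds a plan to look at the programme's association with "survival outcomes especially disease-free survival and discover the potential beneficial population of such intervention". The Discussion states the main objective as improving quality of life "as well as benefiting their survival outcomes especially DFS", and its conclusion promises an evaluation of efficacy on "quality of life and survival outcomes after surgery".
- **Sample size.** The 210 patients (140 and 70) are derived from QLQ-C30 scores. No event count, hazard ratio or power is given for DFS.

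**The concern.** Randomisation separates programme from no programme for six weeks. After that any control may take the same programme, and each control decides. DFS is counted over about three years, so nearly all of its observation time, and every scheduled recurrence visit, comes after the offer opens. The same is true of the CaSUN values at years 1 to 3.

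The stake is what the trial may conclude. Read against the Discussion, a flat DFS result could be reported as showing no survival effect, when it might reflect control uptake, too few events, or both. A difference would be reported as programme versus usual care, when the arms actually compared are immediate offer and optional delayed offer. No later analysis restores a randomised usual-care arm after week 6. Comparing patients by what they received would be confounded, because controls choose whether to take the programme up.

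**Working it through.** **1. The plan's own figure.** The only sample size calculation is for QLQ-C30: means 66.1 and 61.5 (difference 4.6), SD 10, two-sided alpha 0.05, power 80%, allocation 2:1, 15% dropout.

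Controls = (1.96 + 0.8416)² × 10² × (1 + 1/2) / 4.6² = 7.849 × 150 / 21.16 = 55.6, so 56. With 112 in the intervention arm the total is 168, and 168 / 0.85 = 198. The stated 210 is about 6% larger, which is conservative and does not bear on this point. What matters here is that DFS plays no part in it.

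**2. Protected time.** Six weeks out of 3 × 52 = 156 weeks is 3.8% of the DFS horizon.

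**3. Dilution.** Assumptions, none of them from the article: true hazard ratio 0.70; a fraction c of controls takes the programme and gains its full benefit; the six protected weeks are ignored.

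Apparent HR = 0.70 / (1 − c + 0.70c)

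| Control uptake c | Calculation | Apparent HR |
|---|---|---|
| 0% | 0.70 / 1 | 0.70 |
| 25% | 0.70 / 0.925 | 0.76 |
| 50% | 0.70 / 0.85 | 0.82 |
| 70% | 0.70 / 0.79 | 0.89 |

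A second model keeps the control hazard unchanged until week 6 and takes exponential times with 30% three-year recurrence in untreated controls. It gives 0.76, 0.82 and 0.90 at 25%, 50% and 75% uptake, and 0.98 at 100%. Ignoring the six weeks therefore makes little difference.

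**4. Events and power with no uptake (a separate limitation).** Schoenfeld's formula at 2:1, with (2/3)(1/3) = 2/9:

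- Events needed for 80% power at HR 0.70 = 7.849 / [(2/9) × (ln 0.70)²] = 7.849 / (0.2222 × 0.1272) = 278.
- Assumed overall three-year relapse of 15% and 30% gives 210 × 0.15 = 31.5 and 210 × 0.30 = 63 events, with no loss to follow-up.
- Power = Φ(√(events × 2/9) × 0.3567 − 1.96). At 31.5 events: Φ(0.944 − 1.96) = 15.5%. At 63 events: Φ(1.335 − 1.96) = 26.6%.
- HR detectable with 80% power = exp(−2.8016 / √(events × 2/9)) = 0.35 at 31.5 events and 0.47 at 63.

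Taking 15–30% as the control-arm rate instead gives about 26–52 events and 13–23% power.

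**5. Both together.** In the second model of step 3 (N = 210, no loss, HR 0.70), power is about 23%, 15%, 10%, 5% and 3% at uptake of 0, 25, 50, 75 and 100%.

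**6. The aims side by side.** Introduction: survival is additional and worded as an association. Secondary outcomes: DFS is secondary. Discussion: survival benefit is part of the main objective, and the conclusion speaks of efficacy. The article does not agree with itself on how central survival is.

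**The case against.** A reader might infer that the three-year comparisons cannot show any benefit. The article does not support that. Uptake is voluntary and unstated, and partial uptake weakens the as-randomised contrast without voiding it. A DFS difference that emerged despite dilution would still be evidence, and probably conservative. The Discussion cites a study in which more than 60% of colorectal cancer patients were unwilling to join a psychological intervention. That hints at modest uptake, but only indirectly, since controls here have already consented to a trial of such a programme. At 25% uptake the dilution from 0.70 to 0.76 is modest. This objection stands.

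A reader might also carry the problem over to CaSUN as a whole or to the primary outcomes. Neither follows. CaSUN measures unmet needs, not survival, and its values to week 6 are collected while controls have no access. All four primary outcomes end at week 6.

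Three further points are fair. A delayed offer to controls is a common design. A phase II trial need not power a secondary time-to-event endpoint, and low event numbers are a different problem from control uptake. The article already specifies intention to treat, proposes no as-treated analysis, and says session participation will be recorded, though not that this extends to controls who join later. Details of handling may be in a fuller protocol or an SAP.

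What these do not answer is the wording of the Discussion. The delayed offer and the survival objective are both stated in this document, and low uptake would not rescue the objective, because power is already low at zero uptake.

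**Conclusion.** The point holds in a limited form. DFS and the year 1–3 CaSUN values compare an immediate with an optional delayed offer and are diluted toward no difference by an amount the article leaves open. For DFS the size is illustrative: a true hazard ratio of 0.70 would appear as about 0.76 to 0.89 for uptake of 25% to 70%, if uptake brings full benefit. If it brings less, the dilution is smaller. Independently of uptake, 15–30% three-year relapse would give about 16–27% power at that hazard ratio. The hazard ratio, relapse and uptake values are all assumptions.

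It follows that a null DFS result would be uninformative, and that a DFS difference would not estimate programme versus usual care. It does not follow that the comparison is worthless, or that the week-6 conclusions are in doubt. The defect is that the Discussion claims more for survival than the design supports and more than the Introduction and Secondary outcomes sections say.

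**What to change.** 1. Label DFS and the year 1–3 CaSUN comparisons as exploratory, with the contrast named as immediate versus optional delayed offer. Analyse them as randomised, in line with the intention-to-treat principle already stated, and report DFS as a hazard ratio with its confidence interval.
2. Make week 6 the timepoint for the between-arm test of CaSUN. The visit is already in Table 3.
3. For each control who takes up the programme, record the date and the number of sessions attended. Start now, because this is hard to reconstruct later.
4. Reword the main objective and the conclusion in the Discussion to agree with the Introduction and Secondary outcomes sections, with no claim of survival efficacy.

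The offer to controls need not change, and no visit or patient is added. The cost is a change of wording, one extra data field and a less ambitious stated claim.
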